#### Sensitivity analyses

In addition to the main MMRM, ITT analyses using the Jump to Reference (J2R) method [31] and CC analyses will be conducted. For these, change scores from baseline (T0) to follow-up (T2) will be analyzed via analysis of covariance (ANCOVA) with baseline as covariate [32,33]. J2R reflects the treatment policy estimand as defined by the EMA [34].

#### Clinical relevance

Outcomes relevant to medical benefit will be interpreted against established Minimal Clinically Important Difference (MCID) thresholds: ≥8-point increase on the AAQoL [35] and ≥30 % reduction on the ASRS [36].

#### Multiplicity control

A hierarchical testing procedure will be applied. Significance will be declared at each step only if the *p*-value < 0.05 and all preceding tests are significant. The testing order is:1.Quality of life (AAQoL)2.ADHD symptoms (ASRS)3.Global functional impairment (CGI-S)4.Depressive symptoms (PHQ-9)5.Anxiety symptoms (GAD-7)6.Substance use (AUDIT-C)7.Substance use (DUDIT)8.Health literacy (HLS-EU)9.Daily functioning (BFIS)10.Medication adherence (MARS-D)

#### Exploratory analyses

Subgroup analyses will be conducted for primary and secondary outcomes by age (≤65 vs. >65 years), gender (male/female/diverse), current medication status (yes/no), and app use (dichotomized at median module completion). In addition, exploratory analyses will examine changes in perceived self-stigmatization, as measured by the ISMI-9.

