**Fig. 1 fig0001:**
[figure not shown]
Study Flow.

The IG receives immediate access to the 12-week app-based self-help program (ORIKO^Ⓡ^) following baseline, while the CAU group gains access after completion of the final follow-up at T2. All data are collected online.

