### Randomization and blinding

Participants are randomized automatically in a 1:1 ratio (IG vs. CAU) using an algorithm embedded in the online survey platform Qualtrics^Ⓡ^. Randomization occurs after informed consent and completion of the baseline assessment, minimizing allocation bias. Group allocation is disclosed to participants at the end of the baseline survey, as blinding is not feasible: no placebo condition exists, and participants must know whether they receive immediate or delayed access to the app.

Data collection is based entirely on digital self-report questionnaires administered through Qualtrics, eliminating potential assessor bias. Because allocation is automated and outcome scoring is standardized, neither study staff nor data analysis procedures are subject to manipulation.

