### Procedure and assessments

Potential participants are recruited at UKE or via online outreach and receive detailed study information along with a link to the digital informed consent form and baseline survey (T0). After consent, they complete the questionnaires listed in Table 1. Participants are then randomized (see Randomization and Blinding). Those allocated to the IG receive an access code to the app, while the CAU receives access after the final assessment (T2). Identical surveys are administered at 6 weeks interim (T1) and 12 weeks (T2), with the IG additionally completing the CSQ-8 at T1 and T2. At each assessment, medication status and CAU are recorded. Participants are compensated with an online shopping voucher upon completion of follow-up assessments.

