#### Intervention adherence

Engagement with the digital program is tracked descriptively using log-file data (frequency of access and number of completed modules).

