#### Efficacy analyses

Primary efficacy will be evaluated at 12 weeks (T2), defined as the primary endpoint, using mixed models for repeated measures (MMRM), a likelihood-based approach suitable for longitudinal data and missingness under the missing-at-random assumption [29,30]. Models will include fixed effects for group, time, and group × time interaction, with baseline values entered as covariates. A random intercept for participants and an unstructured covariance matrix will be specified. Degrees of freedom will be estimated using the Kenward–Roger approximation.

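### App use, split at median module completion, arises after randomisation and does not exist in the control arm before T2, so it cannot define a treatment-effect subgroup

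*Protocol article*

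**What the plan says.** Under Exploratory analyses the protocol article states: "Subgroup analyses will be conducted for primary and secondary outcomes by age". The same sentence goes on to gender, current medication status and "app use (dichotomized at median module completion". All four factors are presented in the same way. No comparator is named for the two app-use halves, and the result is not restricted to an association within the intervention group (IG).

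Four other places fix when and for whom app use exists:

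- Randomization and blinding: "Randomization occurs after informed consent and completion of the baseline assessment".
- Procedure and assessments: "Those allocated to the IG receive an access code to the app, while the CAU receives access after the final assessment (T2".
- The study-flow text under Fig. 1 says the same of the control arm: "while the CAU group gains access after completion of the final follow-up at T2".
- Efficacy analyses: "Primary efficacy will be evaluated at 12 weeks (T2), defined as the primary endpoint".

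The variable itself is described under Intervention adherence: "Engagement with the digital program is tracked descriptively using log-file data (frequency of access and number of completed modules".

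**The concern.** A subgroup analysis asks whether the randomised contrast differs between types of participant. It needs a factor that is defined in both arms and is not itself a result of allocation. App use meets neither condition. Calling it a subgroup factor promises a treatment effect by level of use that this design cannot supply.

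The practical risk lies in interpretation. The Objectives section frames the trial as an evaluation of medical benefit. A table showing larger gains in heavier users, printed beside genuine subgroups, invites a dose-response reading. The same pattern can arise when people who are going to do better anyway also complete more modules.

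**Working it through.** **Step 1: can the subgroup effect be formed?**

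- Order of events: consent and baseline, then randomisation, then the access code (IG only), then use of the app, then T2. Module completion is therefore a post-randomisation variable.
- CAU gets access only after T2, which is the primary endpoint visit. No CAU participant can have a module count that precedes the endpoint.
- If app use is left undefined in CAU, there is no control group within either level and no interaction term to fit.
- If CAU is coded as zero modules, every control falls in the low-use level and the high-use level contains no controls. The interaction is still not estimable.
- Two contrasts remain: IG-high against IG-low, and either IG half against all of CAU. In both, membership of an IG half is self-selected.

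**Step 2: how large a gap can self-selection produce?**

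Inputs:

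- Design effect *d* = 0.40, two-sided α = 0.05, power 0.90, and 30 % inflation (Sample size section).
- *r*, the within-IG correlation between completion and the baseline-adjusted T2 outcome. The document does not give it. It is assumed here to lie between 0 and 0.4.
- Completion is treated as normally distributed and the outcome SD is set to 1.

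The plan's own figures reproduce. The *t*-test calculation gives 132.3, rounded up to 133 per arm, or 266 in total, and 266 / (1 − 0.30) = 380, or 190 per arm. The point does not depend on these figures; they only set the group sizes used below.

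The mean of a standard normal variable above its median is √(2/π) = 0.798, and below it −0.798. If completion has no effect, each half of IG is shifted by ± *r* × 0.798, and the high-versus-low gap is 2 × *r* × 0.798:

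- *r* = 0: gap 0
- *r* = 0.1: 2 × 0.1 × 0.798 = 0.16 SD
- *r* = 0.2: 2 × 0.2 × 0.798 = 0.32 SD
- *r* = 0.3: 2 × 0.3 × 0.798 = 0.48 SD
- *r* = 0.4: 2 × 0.4 × 0.798 = 0.64 SD

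**Step 3: simulation** (4,000 trials per setting, completion with no causal effect, zero treatment effect). The gaps agreed with the formula. The high-versus-low comparison was nominally significant as follows:

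| *r* | 190 per arm | 133 per arm |
|---|---|---|
| 0 | about 5 % | about 5 % |
| 0.1 | 19 % | 15 % |
| 0.2 | 60 % | 45 % |
| 0.3 | 93 % | 80 % |

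Against all of CAU, with *r* = 0.3 and 190 per arm:

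- True effect 0: high users appear to gain 0.24 SD and low users to lose 0.24 SD.
- True effect 0.40 in everyone: high users show 0.64 SD and low users 0.16 SD, although the effect is the same in both.

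**The case against.** Several points on the other side stand.

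- **The analysis is exploratory.** It lies outside the ten-step hierarchy, the primary model and the sensitivity analyses. It cannot alter the primary estimate or its type I error.
- **A gradient is not certain.** A reader might infer that the analysis is bound to show a spurious dose-response. The document does not support that. The gap requires completion to be related to prognosis, no such figure is given, and at *r* = 0 there is no gap. A negative correlation would reverse it.
- **Baseline adjustment helps.** The planned models adjust for baseline, so any part of the association that runs through the baseline score is removed. The *r* that matters is the one left after adjustment. This is why the sizes above are stated for the baseline-adjusted outcome.
- **A within-IG comparison is legitimate as an association.** The article does not say that the halves will be set against CAU or read causally, and the comparator could be left to the analysis plan. That is fair, but no choice of comparator turns app use into a treatment-effect subgroup, and that is how the sentence lists it.

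Two further inferences are tempting but not supported. One is that the subgroup contradicts the Intervention adherence section ("Engagement with the digital program is tracked descriptively using log-file data"). That sentence describes how engagement is recorded and summarised; it does not forbid a separate exploratory use. The other is that medication status is also a post-baseline factor because it is recorded at all three visits. Which visit defines that subgroup is ordinary analysis-plan detail.

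**Conclusion.** The point holds in a limited form. As listed, app use cannot define a subgroup treatment effect or an interaction. That follows from the stated timing of randomisation and app access and needs no assumption. Any contrast that can be computed is non-randomised.

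The size of the possible distortion does rest on an assumption: 0 / 0.16 / 0.32 / 0.48 SD between high and low users for *r* = 0 / 0.1 / 0.2 / 0.3. Two approximations apply. Completion is a count over 12 modules, so ties will make the split less clean than the normal formula assumes. The gap is in SDs of the baseline-adjusted outcome, so setting it beside the design effect of 0.40 SD shows the order of magnitude only. Even so, a modest correlation is enough to yield a gap of the size the trial seeks.

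A reader might infer that the trial's main conclusion is at risk. It is not: the confirmatory testing does not use this variable. The flaw is confined to an exploratory analysis and is best corrected before outcome data are seen.

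**What to change.** Remove app use from the list of treatment-effect subgroups. Report module completion within IG only, as a baseline-adjusted descriptive association with T2 outcomes, and state that it is non-causal.

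If an adherence effect is wanted, pre-specify a randomisation-based estimand with its assumptions. Two options are:

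- Subgroups by predicted completion: model completion in IG from T0 covariates, apply the prediction to both arms, and compare the arms within predicted levels. This depends on T0 data predicting completion usefully.
- A complier-average causal effect with allocation as the instrument and compliance defined as any app use. It should not be defined by the median split, because below-median users also receive modules and the exclusion restriction would then fail. Even with any use as the definition, the restriction has to be argued, since the Limitations section acknowledges expectancy effects from the lack of blinding.

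The cost is a change of wording and, if an adherence estimand is added, a little analysis work. The log files and T0 assessments already planned supply the data.

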### Patient safety

At each assessment (baseline and follow-ups), participants are provided with the contact details of the study team and may reach out at any time in case of symptom deterioration, unexpected negative experiences or study-related questions. Adverse events are not assessed using a standardized questionnaire. Instead, potential adverse effects are monitored through participant-initiated contact with the study team and are documented as part of ongoing study monitoring. Participants remain fully embedded in the regular healthcare system in Germany, and participation does not restrict access to treatment as usual, including mental health care. Given the low-risk, self-guided nature of the digital intervention and the absence of medical procedures, no independent data monitoring committee was established.

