#### Depressive symptoms

The Patient Health Questionnaire-9 (PHQ-9) [12] measures depressive symptoms over the past two weeks with nine items rated from 0 (not at all) to 3 (nearly every day). Total scores range from 0 to 27 and can be categorized into minimal, mild, moderate, and severe depression. Reliability is high (Cronbach’s α = 0.89).

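### Adverse events are captured only when a participant makes contact, so in this open-label trial the counts are likely incomplete and may not be comparable between arms

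*Protocol article*

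**What the plan says.** The Patient safety section of the protocol article makes an explicit choice: "Adverse events are not assessed using a standardized questionnaire". The only route it describes relies on the participant to start the exchange: "potential adverse effects are monitored through participant-initiated contact with the study team". What arrives this way is then documented. All participants receive the team's contact details at baseline and at both follow-ups, and are told they may get in touch about worsening symptoms or unexpected bad experiences. The section adds that "no independent data monitoring committee was established", which it justifies by the low-risk, self-guided nature of the app.

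Three other places bear on this:

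- Randomization and blinding: "Group allocation is disclosed to participants at the end of the baseline survey, as blinding is not feasible".
- Procedure and assessments: "Identical surveys are administered at 6 weeks interim (T1) and 12 weeks (T2), with the IG additionally completing the CSQ-8 at T1 and T2". Table 2 shows that AAQoL, ASRS, CGI-S, PHQ-9, GAD-7 and AUDIT-C/DUDIT are collected at T0, T1 and T2.
- Hypotheses and Clinical relevance: the scales enter as efficacy outcomes, and the two stated thresholds (8 points or more on the AAQoL, 30% or more on the ASRS) are for improvement.

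**The concern.** A spontaneous report needs two things: an event, and a decision to write to the team. Only the first is a property of the treatment. The second can depend on the arm, because participants know what they were given. Someone using a new app has something to which a bad experience can be attributed; someone waiting for access does not. Equally, app users may treat discomfort as part of the programme, while disappointed waitlist participants may be readier to complain. The documents do not settle which effect is larger.

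The recorded count is therefore the product of a harm rate and an unknown, possibly arm-dependent, reporting rate, and the two cannot be separated afterwards. No analysis plan can recover reports that were never solicited. What is at stake is what can later be said about harms beside a result on medical benefit, which is the primary objective. The efficacy analysis itself is not affected.

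**Working it through.** **The plan's own figure.** The only design figure needed is the number per arm. An exact two-sided t-test with d = 0.40, α = 0.05 and power 0.90 requires 132.3, so 133 per arm and 266 in total. Dividing by (1 − 0.30) gives 266 / 0.70 = 380, or 190 per arm. Both figures in the Sample size section reproduce.

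**Inputs for the illustration.** n = 190 per arm is from the Sample size section. All harm and reporting rates below are assumptions, because the documents give none.

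**Formula.** Expected recorded events = n × true rate × reporting rate.

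1. *Under-ascertainment.* With 5% worsening, 190 × 0.05 = 9.5 true events per arm. At 10% reporting, 9.5 × 0.10 = 0.95 are recorded; at 30%, 9.5 × 0.30 = 2.85.

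2. *Arm-dependent reporting.*

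| True rate IG / CAU | Reporting IG / CAU | Recorded IG / CAU | Recorded ratio |
|---|---|---|---|
| 10% / 10% | 50% / 50% | 9.5 / 9.5 | 1.0 |
| 10% / 10% | 30% / 10% | 5.7 / 1.9 | 3.0 |
| 10% / 10% | 50% / 20% | 9.5 / 3.8 | 2.5 |
| 10% / 10% | 20% / 50% | 3.8 / 9.5 | 0.4 |
| 10% / 5% | 20% / 40% | 3.8 / 3.8 | 1.0 |

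The same mechanism can create a difference, reverse its direction or hide a true doubling.

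3. *Equal reporting still loses information.* Power = Φ{[|p₁ − p₂| − 1.96·√(2p̄(1 − p̄)/n)] / √([p₁(1 − p₁) + p₂(1 − p₂)]/n)}. For true rates of 20% and 10% with complete capture and n = 190: (0.100 − 1.96 × 0.03664) / 0.03627 = 0.78, and Φ(0.78) ≈ 0.78. With 30% reporting in both arms the rates become 6% and 3%: (0.030 − 1.96 × 0.02127) / 0.02121 = −0.55, and Φ(−0.55) ≈ 0.29.

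4. *What a survey question could deliver.* The Sample size section expects about 25% attrition and allows for 30%, which leaves about 142 (190 × 0.75 = 142.5) or 133 (190 × 0.70) respondents per arm. If respondents answer fully and have the same true rates of 20% and 10%, power is about 0.66 or 0.63. For a rate of 10% in both arms, the 95% half-width of the risk difference is 1.96 × √(2 × 0.10 × 0.90 / 142) = 0.070, or 0.072 with 133. This is imprecise, but it has a known denominator and the same question in both arms.

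**What the planned analyses already show.** The MMRM and ANCOVA estimate group differences, and the sample size is based on a two-tailed test. If the intervention arm worsened on average on PHQ-9, GAD-7, ASRS, CGI-S, AUDIT-C or DUDIT, the estimate would have the wrong sign. What a mean cannot show is a minority who worsen while the arm improves on average. The article states no outcome that counts such participants.

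**The case against.** The strongest defence is that the choice is open and reasoned. The intervention is a self-guided app without medical procedures, participants stay in regular care, and contact is invited in both arms at every assessment. No comparative safety claim appears in the objectives, the hypotheses, the testing order or the conclusion, so no planned inference is spoiled. Deterioration rates are an analysis definition that may stand in the SAP, which the article says is accessible in the registry and which is not at hand here. A new survey item would not reach those who stop answering, and in an open-label trial it too remains open to attribution by arm.

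Most of this stands, and it limits the point. A reader might infer four stronger things that the article does not support:

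- *That safety cannot be compared at all, or that only improvement is analysed.* Average worsening would be visible in the planned comparisons.
- *That the count will be close to zero.* This depends on reporting rates that nobody has stated.
- *That the app arm will over-report, or that worsening dropouts are the least likely to write in.* Both are plausible but undocumented, and the opposite direction is just as easy to construct.
- *That a planned safety conclusion is invalid.* None is planned.

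What does not stand is the low-risk argument as an answer to ascertainment. The article uses it to explain the absence of a monitoring committee. It does not make unsolicited counts complete or comparable. An invitation to make contact is also still passive: silence cannot be told apart from no event.

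**Conclusion.** The point holds in a limited form. Participant-initiated capture in a trial with known allocation gives adverse-event counts that are likely incomplete and may not be comparable between arms, with bias of unknown direction. The Limitations section mentions expectancy effects and self-report bias for outcomes, but not this. The size cannot be estimated from the documents. Under the assumed rates, equal true harm can appear as a ratio anywhere from 0.4 to 3.0, and a true doubling can disappear. The primary efficacy result is untouched; the limit falls on what can later be reported about harms. This is an inexpensive improvement worth making, not a defect in the confirmatory analysis.

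**What to change.** 1. Add one question on new or worsened problems, worded identically, to the T1 and T2 surveys of both arms. Report the answers by arm with the number of respondents as denominator, and report spontaneous contacts separately.

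2. As a supporting analysis, unless the SAP already defines one, report by arm the proportion who deteriorate on AAQoL, PHQ-9 and ASRS, with risk difference and 95% confidence interval. Fix the thresholds in advance. An AAQoL decrease of 8 points or more is one candidate; it is proposed here as a mirror, since the Clinical relevance section sets 8 points for improvement only. Thresholds for PHQ-9 and ASRS would need to be defined.

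3. State in Limitations that spontaneous reports are incomplete and may differ by arm, and that participants who do not answer at T1 or T2 remain unobserved under either approach.

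Cost: the first step needs a survey amendment, lengthens the surveys slightly and puts more events on record. The second needs no new data. If recruitment is too far advanced for the first step, the second and third remain available.

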### Comparison to prior work

Previous research on digital interventions for ADHD in adults remains limited. While pilot trials and small-scale feasibility studies have suggested improvements in quality of life, ADHD symptoms, and functional outcomes, few randomized controlled trials have been conducted to date. The present study builds on this early evidence by implementing a larger RCT with a comprehensive assessment strategy, thereby extending prior work and addressing the need for robust data on the clinical utility of digital health applications in ADHD.

### Strengths

Key strengths of the study include its randomized controlled design, preregistration, and use of validated outcome measures across multiple domains of functioning. Another strength is that ADHD diagnoses are verified by trained study staff prior to enrollment, ensuring diagnostic accuracy and reducing the risk of including ineligible participants. The entirely digital recruitment, intervention, and assessment process supports feasibility, scalability, and broad accessibility. In addition, both intention-to-treat and sensitivity analyses are planned, strengthening the robustness of the findings.

## Protocol validation

De-identified data generated during the study will be made available upon reasonable request to the corresponding author, in line with data protection regulations and institutional policies.

## Limitations

Some limitations should be considered. Participant blinding is not feasible due to the nature of the digital intervention and the waitlist control with CAU design, which may introduce expectancy effects. Outcomes are assessed exclusively via self-report, which may be subject to reporting bias. In addition, recruitment and adherence may be challenging, as digital interventions for ADHD can be associated with higher attrition rates. Although the waitlist design ensures that all participants eventually receive access to the intervention, it may raise ethical considerations related to delayed treatment for participants assigned to the control condition. This concern is mitigated by the relatively short waiting period, and the fact that participation does not restrict access to care as usual. Finally, the fully digital and self-guided format limits personal contact, which may affect engagement for some participants.

